**Data collection and analysis**

Sociodemographic data and clinical variables will be collected by clinical interview and by accessing the electronic history of the patient. The questionnaires as well as the EMGs will be obtained before the treatment, at the end of the treatment and at 6 months. Both the participants and the outcome assessors will be unaware of the allocation to each of the treatment arms. Primary outcomes will be obtained by intention-to-treat analysis.

Descriptive statistics will be obtained by expressing continuous variables as mean (standard deviation) or median (quartiles) according to their normality or not, categorical variables in number (percentage) and expressing in all cases the 95% confidence interval. The normal distribution will be verified by the Kolmogorov test to determine the use of parametric or non-parametric tests. For comparison of continuous variables between groups, the Student's t tests or the Mann-Whitney U tests will be used and for categorical variables the Chi-square or Fisher's test according to the type of distribution. Intragroup changes in continuous variables at the end of treatment and at 6 months will be analyzed with Student's t test for paired samples. To assess whether there are differences between the two groups in pain, disability and in the different variables, analysis of covariance (ANCOVA) will be performed, one for each dependent variable. In all the tests, the independent variable will be the group while the covariate variable will be the baseline level of each dependent variable. It will be necessary to have comparable levels in both groups to correctly interpret the ANCOVA results. Therefore, several Student's t tests will be performed, one for each dependent variable, considering each group as an independent variable in each case. To assess whether the changes in the 2 groups occur differently, several ANOVAs will be performed, one analysis for each dependent variable. In all cases, the independent variable will be the group and the time in which the data are collected. In this analysis, only the possible presence of interactions is studied. In addition, the correlations between the study variables will be evaluated using Pearson's r or Spearmann's Rho according to normality. Two models of multiple linear regression will also be applied with pain and disability as dependent variables and in both models age, sex, pain, catastrophization, fear-avoidance, sick leave, evolution time and anxiety-depression as independent variables.

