**METHODS**

**Design**

Randomized, double-blind clinical trial, with 2 arms (VNM, Vplacebo), 3 assessing times (pre-treatment, at the end of treatment and follow-up at 6 months) and intention-to-treat analysis.

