**Power and sample size**

The study has been planned to obtain a difference of 3 points in the Roland Morris questionnaire since these values have been recognized as clinically relevant (18,19). According to the results of a previous sample of patients with CMLBP obtained in our center, the mean disability measured by the RM questionnaire had a SD of 3.2. Considering an alpha value of 0.05 and beta of 0.9 for comparison of two-tailed means, the required sample size is 24 patients per group to detect changes in disability. Considering losses of 20%, the study sample is established in 62 patients (20).

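### The group-by-time ANOVA has no patient term although each patient is measured three times; as worded it is far too conservative, and the classical repeated-measures alternative fits poorly with 20% planned losses.

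*Protocol*

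**What the plan says.** Under Design, the protocol sets "3 assessing times (pre-treatment, at the end of treatment and follow-up at 6 months) and intention-to-treat analysis". Data collection and analysis repeats the principle: "Primary outcomes will be obtained by intention-to-treat analysis". The same section names three kinds of comparison over time:

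- paired t tests for change within each group, at end of treatment and at 6 months;
- an ANCOVA per outcome, with group as factor and the baseline value as covariate; no visit is named;
- an ANOVA per outcome to see whether the groups change differently, in which "the independent variable will be the group and the time in which the data are collected". Only the interaction is to be read.

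Power and sample size fixes the target: "The study has been planned to obtain a difference of 3 points in the Roland Morris questionnaire". It adds: "Considering losses of 20%, the study sample is established in 62 patients". The protocol has no rule for missed visits. It does not say that patients who miss a visit are left out.

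**The concern.** Three scores from one patient are correlated. An ANOVA with only group and time as factors treats them as independent and tests the interaction against an error term that includes the variation between patients. A comparison of changes over time should exclude that variation. The test is then too conservative, and a real difference in course can be missed.

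The natural repair, a classical repeated-measures ANOVA, raises another difficulty. It needs all three visits, so a patient lost before 6 months also loses the end-of-treatment value. That fits poorly with intention-to-treat and an expected loss of one patient in five.

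On either reading, the interaction over three visits has 2 degrees of freedom. It says whether the courses differ somewhere, whereas the main objective asks about short-term and medium-term efficacy separately.

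**Working it through.** **Inputs from the protocol.** Difference 3 points; "the mean disability measured by the RM questionnaire had a SD of 3.2"; two-sided alpha 0.05; power 0.90 (printed as a beta of 0.9); 24 per group; 62 in total; 20% losses; three visits. The protocol gives no within-patient correlation, so ρ = 0.3, 0.5 and 0.7 are assumptions.

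**The plan's own figure.** n = 2(1.960 + 1.282)² × 3.2² / 3² = 23.9, so 24 per group, as stated. Inflation: 48 / 0.8 = 60. With the t-based size, 24.9 / 0.8 = 31.1 per group, about 62 in total. The figure reproduces. After losses, 62 × 0.8 = 49.6 patients remain, about 25 per arm. Power is then still about 0.90, so the allowance for losses protects precision.

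**Reading 1: group and time only.** Assume equal variances σ² = 3.2² = 10.24 and a common correlation ρ. Under no effect:

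- interaction mean square: expectation σ²(1 − ρ);
- residual mean square without a patient term: expectation σ²;
- so the F ratio is too small by a factor of about 1 − ρ.

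With 25 per arm, the 5% critical value of F on 2 and 6 × 25 − 6 = 144 df is 3.06. The true type I error is roughly P(F > 3.06/(1 − ρ)) ≈ exp(−3.06/(1 − ρ)):

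- ρ = 0.3: exp(−4.37) = 1.3%
- ρ = 0.5: exp(−6.12) = 0.2%
- ρ = 0.7: exp(−10.2) = below 0.01%

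For power, take a 3-point difference at both later visits. The interaction deviations are ±1, ±0.5 and ±0.5, with sum of squares 2(1 + 0.25 + 0.25) = 3. The noncentrality is 25 × 3 / [10.24(1 − ρ)], that is 10.5, 14.6 and 24.4. A simulation of 2,000 trials with 25 per arm gives:

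| ρ | Type I error, no patient term | Type I error, patient term | Power, no patient term | Power, patient term |
|---|---|---|---|---|
| 0.3 | 1.7% | 4.9% | 67% | 82% |
| 0.5 | 0.2% | 4.8% | 70% | 94% |
| 0.7 | 0.0% | 4.4% | 70% | 99% |

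With 24 per arm, power is about 65% without and 81 to 99% with the patient term.

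**Reading 2: classical repeated-measures ANOVA.** The error term is right, but the analysis keeps only patients with all three visits. If the 20% losses all fall between end of treatment and 6 months (an assumption), 62 × 0.2 = 12.4, so about 12 patients who supplied an end-of-treatment score are removed.

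**Bias at 6 months.** An ANCOVA without imputation uses patients seen at that visit. A 2,000-trial simulation took 31 per arm, 6 lost per arm, ρ = 0.6 and a true difference of −3:

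| Assumed dropout rule | ANCOVA estimate | Bias |
|---|---|---|
| Same rule in both arms | −2.99 | about 0 |
| Only placebo losses depend on the end-of-treatment score | −2.74 | about 0.25 |
| Arms lose opposite tails of that score | −2.48 | about 0.5 |

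The largest bias is 0.5/3 = 17% of the target. A likelihood analysis that also uses the end-of-treatment score stays within 0.02, because dropout was generated from that score. Dropout that depends on the unseen 6-month value was not examined.

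**The case against.** A reader might infer that the protocol promises intention-to-treat but delivers a completers' analysis. The document does not support this. It specifies no complete-case rule. Analysing patients as randomised is compatible with ANCOVA, paired t tests and ANOVA, and imputation could come first. Missing-data handling is commonly left to the SAP, and the 20% allowance does not define an analysis set.

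Nor do all the named methods drop patients. An ANOVA without a patient term uses every available record. The ANCOVA and paired t tests omit a patient only at the missed visit. Deletion of the whole patient belongs to Reading 2, so the two criticisms of the ANOVA are alternatives and cannot be added together.

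It can also be said that the sentence is loose or translated wording for a mixed ANOVA, that the ANOVA merely supplements the ANCOVA, that its error is conservative and creates no false claim of efficacy, and that the bias figures rest on invented dropout. Much of this stands. The section does recognise pairing in its t tests, so a within-patient factor may be intended. The worst bias, 0.5 points, is below one standard error of the ANCOVA estimate: 3.2 × 0.8 × √(2/25) = 0.72.

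What remains is that the text as written gives a wrong test, and that the likely intended test handles missed visits badly. The ANCOVA does not clearly fill the gap, since no visit is named for it.

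**Conclusion.** The point holds for the ANOVA. Followed literally, its interaction test has a type I error of about 0 to 2% instead of 5%. Its power for 3 points is about 65 to 70%, where a correct error term gives about 81 to 99%. These figures assume correlations of 0.3 to 0.7, equal variances, 24 to 25 patients per arm and the same 3-point difference at both later visits. If a classical repeated-measures ANOVA is meant, the test is valid for complete patients but discards those with one missed visit, and it still gives no estimate at either time point.

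The 6-month bias is a possibility only: zero under a common dropout rule, and about 0.25 to 0.5 points under unfavourable arm-specific rules that the protocol does not predict. No breach of intention-to-treat is shown. The plan should be changed because a better-matched analysis is available at low cost.

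**What to change.** Replace the ANOVA, and make the between-group analysis one mixed model for repeated measures per outcome:

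- responses: the end-of-treatment and 6-month values;
- fixed effects: baseline, group, visit, group × visit and baseline × visit;
- unstructured within-patient covariance;
- all randomised patients with any post-baseline value, analysed as allocated.

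Report the group difference at each visit with its 95% CI. Add one sensitivity analysis for departures from missing-at-random, for example by shifting the missing values by a stated delta.

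This needs revised analysis wording and slightly more programming, and no new data. The model relies on missing-at-random, hence the sensitivity analysis. It still omits patients with no post-baseline value, whose number should be reported by arm.

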**TREATMENT WITH NEUROMUSCULAR BANDAGE IN CHRONIC MECHANICAL LOW BACK PAIN. RANDOMIZED CLINICAL TRIAL.**

**ABSTRACT**

**Objectives.** To assess the efficacy of neuromuscular bandage (NMV) treatment on pain intensity, disability and quality of life in patients with chronic mechanical low back pain (CMLBP). The secondary objectives of the study are to evaluate the effect of treatment with VNM on the neuromuscular activity pattern of the extensor muscles of the trunk, abdominals and hamstrings and to analyze the influence of fear-avoidance beliefs, ideas of catastrophization, and presence of anxiety-depression in the efficacy of NMV in the treatment of these patients.

**Methods.** This is a randomized clinical trial in 62 patients with CMLBP, recruited from a specialized rehabilitation medical practice. Participation in the study will be offered consecutively to all those patients in whom the mobilization of skin / fascia in the clinical examination is shown as a "modifying factor of the effect of the treatment". They will be assigned randomly and with concealment of the randomization sequence to two intervention groups: the VNM group and the placebo bandage group. The duration of treatment will be 4 weeks, changing the bandage 4 times, weekly. In evaluating the results, on the one hand, alterations in the muscle activity patterns of the trunk extensors, obtained by surface electrode electromyography (SEMG), will be taken into account. On the other hand, data will be obtained by clinical interview and the use of validated questionnaires: Numerical Pain Scale (NPS), Roland-Morris Questionnaire (RM), SF-36, Fear Avoidance Beliefs Questionnaire (FABQ), Hospital Anxiety and Depression subscale (HAD) and Pain Catastrophization Scale (PCS). The assessment will be carried out in 3 evolutionary moments: pre-intervention, post-intervention and at 6 months. Both patients and evaluators will remain blind to the assigned treatment.

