**Intervention**

Patients who agree to participate in the study will be randomly assigned to one of the two intervention groups. The assignment will be made by a computer-generated list (SPSS 19 program), balancing the participants between the groups according to the degree of baseline disability at study entry, and the randomization being supervised by a statistician outside the research team. The randomization sequence will be concealed.

The NMV group will receive treatment with 5 cm wide NMV, applied according to the clinical examination, based on the following guideline: If the lumbar pain in flexion or extension improves a) when mobilizing the skin / fascia longitudinally to the paravertebral musculature, the muscular technique will be applied, with the base positioned in the sliding direction, without tension and in a position of maximum lumbar flexion possible, b) when mobilizing the skin / fasciae in approximation towards a point, the technique of space (or ligament), with approximately 75% tension and in a position of maximum possible lumbar flexion, c) when mobilizing the skin / fasciae transversely to the paravertebral musculature, the fascia technique will be applied, in a position of maximum flexion lumbar possible (several techniques can be combined, depending on the examination).

In the placebo group, the same bandage will be applied but in a neutral body position, without tension and applied transversely at a vertebral level that is not painful on palpation (12).

The duration of treatment will be 4 weeks, changing the bandage 4 times, weekly.

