**Outcome measures**:

The following variables will be taken into account in the clinical trial:

- Sociodemographic data: age, sex, profession (classification according to CNAE), sedentary lifestyle (sedentary, sedentary with walking, light or intense physical effort), sporting activity (no sport, low-impact sport, high-impact sport; weekly frequency).

- Clinical variables: weight and height (BMI), process evolution time (in months), previous pharmacological treatment (type, dose, duration), previous physical treatment (type, duration), complementary examinations (Rx, CT, MRI)

- Evaluation of results:

Currently, there is consensus regarding the basic variables to be considered in the evaluation of results in the treatment of low back pain: pain, specific functional limitation due to low back pain, quality of life, work disability and satisfaction (22,23,24). Based on these consensuses, in the evaluation of results we will take into account the following variables:

- Pain intensity: Numerical Pain Scale (NPS), preferable to the visual analog scale because it is less abstract and easier to understand (24).
- Study of SEMG of lumbar spinal erectors, oblique / transverse abdominals, and hamstrings. The muscle activation pattern will be studied descriptively, checking the presence or absence of relaxation in maximum flexion. The pre and post-treatment patterns will be compared again, checking the existence or not of relaxation, and using averages and ratios of electromyographic activity.

• Limitations of the activity: validated version in Spanish of the Roland-Morris Questionnaire (RMQ), useful in situations of mild and moderate disability, more typical of the population usually attended in the MFyRHB consultations (25,26,27,28).

• Quality of life: validated Spanish version of the SF-36 questionnaire (29).

• Work situation: active in their usual job, active in a restricted job, Temporary Disability, Permanent Disability, unemployed due to health problems, unemployed for other reasons, student, housewife, retired (22).

• Fear-avoidance beliefs: validated Spanish version of the Fear Avoidance Beliefs Questionnaire (FABQ) (30,31) that measures beliefs and attitudes regarding the potential effect of work and physical activity on pain.

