• Anxiety and depression: validated Spanish version of the Hospital Anxiety and Depression subscale (HAD) questionnaire (32,33,34) with demonstrated utility in screening for the possible presence of anxiety and depression states.

• Ideas of Catastrophizing in the face of pain: validated Spanish version of the Pain Catastrophizing Scale (PCS), which comprises 3 dimensions: rumination, magnification and hopelessness in the face of pain (35,36).

• Comorbidities: Charlston Comorbidity Index (37).

• Co-interventions: Parallel treatments that the participants may receive (other physiotherapeutic, pharmacological treatments, disc, facet or epidural infiltrations, TENS, electrotherapy or surgery) will be recorded.

• Adverse effects: adverse effects that occur during treatment will be recorded.

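### The protocol wrongly makes interpretation of each baseline-adjusted ANCOVA depend on baseline t tests showing comparable groups

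*Protocol*

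**What the plan says.** Under Data collection and analysis, the protocol assesses differences between the two arms in this way: "analysis of covariance (ANCOVA) will be performed, one for each dependent variable". Group is the factor, and "the covariate variable will be the baseline level of each dependent variable". It then sets a condition: "It will be necessary to have comparable levels in both groups to correctly interpret the ANCOVA results". The next sentence says how the condition is checked: "Therefore, several Student's t tests will be performed, one for each dependent variable, considering each group as an independent variable in each case". That sentence does not use the word baseline, but it is drawn as a consequence of the comparability requirement and has no other sensible reading.

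The section gives no significance threshold for these t tests, no count of dependent variables, and no action if a test is significant. Under Intervention, allocation is by a concealed computer-generated list, "balancing the participants between the groups according to the degree of baseline disability at study entry".

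**The concern.** Equal baseline means are not an assumption of ANCOVA. With concealed random allocation, any difference in baseline means is due to chance, and including the baseline value as a covariate is how the analysis allows for it. A significance test of baseline difference asks whether chance produced the difference, which the design has already answered.

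The t tests therefore carry no information about whether the ANCOVA is valid, yet the protocol makes correct interpretation depend on them. The condition applies to the analysis that compares the arms on pain, disability and quality of life, the three components of the main objective. Only disability is balanced by the allocation, so pain and quality of life remain open to a chance flag. Because no consequence is fixed, the team would decide what a significant baseline test means for an outcome with the results in view.

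**Working it through.** **Inputs from the protocol.** Total sample 62, so 31 per arm if allocation is 1:1. Power and sample size gives a two-tailed alpha of 0.05 for the main comparison. The same level is assumed here for the baseline t tests, because none is stated for them.

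**The protocol's own figure.** There is none for this rule. The sample size does reproduce: with a difference of 3, SD 3.2, and the 0.9 given for beta read as power, 2 × (3.2 × (1.960 + 1.282) / 3)² = 23.9, so 24 per group. Allowing for 20% losses, 48 / 0.8 = 60, close to the stated 62.

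**Does a significant baseline test affect the ANCOVA?** Under the usual linear model the ANCOVA test holds its nominal level given the observed baselines, and hence given any test computed from them. A simulation with no treatment effect (31 per arm, 400,000 trials for each baseline-to-outcome correlation) agrees:

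| Correlation | Baseline test | ANCOVA type I error | Change-score type I error |
|---|---|---|---|
| 0.5 | not significant | 5.0% | 4.3% |
| 0.5 | significant | 5.2% | 18% |
| 0.7 | not significant | 5.1% | 4.7% |
| 0.7 | significant | 5.1% | 13% |

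The mean error of the ANCOVA estimate was within 0.002 SD in all four rows. The last column is the unadjusted change-score comparison, which equals the group-by-time interaction with two time points. Unlike the ANCOVA, it is disturbed by baseline imbalance.

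**What imbalance does cost.** The ANCOVA variance is proportional to 2/n + d²/Sxx, where d is the baseline difference and Sxx the within-group sum of squares. Since d² = t² × (2/n) × Sxx/(2n − 2), the variance is multiplied by 1 + t²/(2n − 2). At the edge of significance with n = 31, t = 2.00, which gives 1 + 4.00/60 = 1.067. The standard error rises by about 3%, and the confidence interval already includes this.

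**How often would the rule be triggered?**

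- For one outcome: 5% at the assumed alpha, and less for Roland-Morris.
- For pain and quality of life, one score each and independent: 1 − 0.95² = 9.75% for at least one flag.
- Across all outcomes, the count must be assumed. The Abstract names six questionnaires: "Numerical Pain Scale (NPS), Roland-Morris Questionnaire (RM), SF-36, Fear Avoidance Beliefs Questionnaire (FABQ), Hospital Anxiety and Depression subscale (HAD) and Pain Catastrophization Scale (PCS"). Splitting FABQ into work and physical activity, HAD into anxiety and depression, and PCS ("which comprises 3 dimensions: rumination, magnification and hopelessness in the face of pain") gives 6 + 1 + 1 + 2 = 10. Adding one measure for each of three muscle groups ("Study of SEMG of lumbar spinal erectors, oblique / transverse abdominals, and hamstrings") gives 13.

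The chance of at least one flag is 1 − 0.95^k for independent outcomes, and is simulated for equal pairwise correlation:

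| Outcomes (k) | Independent | Correlation 0.5 | Correlation 0.7 |
|---|---|---|---|
| 6 | 26.5% | 21% | 17% |
| 7 | 30.2% | 23% | 18% |
| 13 | 48.7% | 34% | 25% |

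Leaving out Roland-Morris, k = 5 to 12 gives 22.6% to 46.0% if independent.

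**The case against.** The strongest reply is that no harm is written down. The ANCOVA is still performed for every dependent variable, and the protocol does not say that a flagged one will be dropped or replaced. A reader might infer that the adjusted analysis would be set aside in favour of another. The documents do not support that: they speak only of correct interpretation, and the group-by-time ANOVA is planned in its own right, not as a fallback. The 18% and 13% above would matter only if someone chose to retreat to it.

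A second inference is that a fifth to a half of such trials would be compromised. That does not follow either. The tests are paired with the ANCOVAs outcome by outcome, and nothing lets a flag on one outcome affect another. The upper end needs about 13 independent outcomes, which is implausible for subscales of the same questionnaire. The protocol also does not say that subscales are separate dependent variables. Part of the SEMG assessment is presence or absence of relaxation, to which a t test does not apply.

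Third, one might call the disability test empty because allocation is balanced on it. Balancing makes a flag unlikely, not impossible.

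Finally, a statistical analysis plan could say how baseline comparisons are used. It could, but the protocol makes a positive statement that is wrong, and a plan that ignored it would contradict the protocol.

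These replies limit the size of the problem. None of them defends the precondition itself.

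**Conclusion.** The rule is wrong as written. Comparable observed baselines are not needed to interpret a baseline-adjusted ANCOVA in this randomised design, and a baseline t test cannot show whether that ANCOVA is valid. This conclusion does not depend on the flag rates.

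Its practical reach is modest. Any one outcome would be labelled not correctly interpretable in about 5% of trials, and Roland-Morris, which sets the sample size, less often. The any-outcome chance of roughly 17% to 34% describes how often the team would face the question somewhere, given 6 to 13 outcomes, alpha 0.05 and correlations of 0.5 to 0.7, none of which the protocol fixes for these tests. The ANCOVA results themselves are not biased by the rule. The damage would come from how they are described, or from a choice of analysis made after seeing the data. This deserves correction but is not among the most serious kinds of fault.

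**What to change.** Under Data collection and analysis, delete the sentence "It will be necessary to have comparable levels in both groups to correctly interpret the ANCOVA results" and the one that follows from it, "Therefore, several Student's t tests will be performed, one for each dependent variable, considering each group as an independent variable in each case". Replace them with wording such as: *Baseline variables will be summarised by arm. The baseline-adjusted ANCOVA will be interpreted whatever the observed baseline difference.*

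If a check of ANCOVA assumptions is wanted, a descriptive look at whether the baseline slopes are parallel in the two arms would be relevant, but it is optional.

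The cost is an edit of two sentences. It needs no extra patients, data or analysis, and it removes one set of tests. It should be made before allocation is revealed to the analysts, so that no interpretive choice depends on the results.

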**OBJECTIVES**

- Main objective: To evaluate the short and medium term efficacy of NMV treatment in pain, disability and quality of life in patients with CMLBP, through a controlled and randomized study.

- Secondary objectives: 1) To evaluate the effect of NMV treatment on the muscle activity patterns of the trunk, abdominal and hamstring extensors obtained by electromyography with surface electrodes. 2) To analyze the influence of fear-avoidance beliefs, of catastrophizing ideas, of the presence of anxiety-depression, and of pain-coping strategies on the effectiveness of the VNM in the treatment of patients with CMLBP.

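### No stated analysis tests whether psychological factors modify the bandage's effect, so secondary objective 2 goes unanswered (SHOULD-FIX)

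*Protocol*

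**What the plan says.** **The question.** Under Objectives, the protocol's second secondary objective begins "To analyze the influence of fear-avoidance beliefs, of catastrophizing ideas, of the presence of anxiety-depression" and ends "of pain-coping strategies on the effectiveness of the VNM in the treatment of patients with CMLBP". The abstract states the same objective without coping.

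**The regressions.** Under Data collection and analysis: "Two models of multiple linear regression will also be applied with pain and disability as dependent variables", with "in both models age, sex, pain, catastrophization, fear-avoidance, sick leave, evolution time and anxiety-depression as independent variables".

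**The other analyses in that section.**
- ANCOVA, one per outcome: "the independent variable will be the group while the covariate variable will be the baseline level of each dependent variable".
- ANOVA, one per outcome: "the independent variable will be the group and the time in which the data are collected", followed by "In this analysis, only the possible presence of interactions is studied".
- Pearson or Spearman correlations among the study variables, with no mention of arm.

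**Timing.** "The questionnaires as well as the EMGs will be obtained before the treatment, at the end of the treatment and at 6 months". The regression sentence does not say which visit supplies the outcomes or the predictors.

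**The concern.** The effectiveness of the bandage is a contrast between two arms. To say that catastrophizing influences it, one must show that the contrast differs between patients with high and low catastrophizing. That requires a model containing group, the factor and their product. None of the stated analyses contains all three.

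At stake is how the secondary results can be read. A clear catastrophizing coefficient in the listed regression would mean that catastrophizing goes with worse pain or disability. It would say nothing about who benefits from the bandage, although the objective invites that reading. An analysis plan that followed the protocol's covariate list would inherit the gap.

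There are two smaller defects in the same place. Pain is a predictor in both models, including the one in which it is the outcome, and neither pain term has a time point. Coping is named in the objective, but no listed measure is described as a coping instrument.

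**Working it through.** **1. Which stated analysis could estimate a group-by-factor interaction?**

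| Analysis | Group | Psychological factor | Group × factor |
|---|---|---|---|
| Two multiple regressions | no | yes | no |
| ANCOVAs | yes | no (own baseline only) | no |
| ANOVAs | yes | no (time only) | no (group × time) |
| Correlations | no | yes | no |

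An ANCOVA or ANOVA with a psychological scale as its outcome asks whether the bandage changes that scale, which is a different question.

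**2. What a regression without group estimates.** Let the factor's slope be b_V under the bandage and b_P under placebo. If both arms are fitted together with 1:1 allocation, the slope estimates (b_V + b_P)/2. Effect modification is b_V − b_P. The first does not determine the second:

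- Slopes 1 and 1: average 1, modification 0.
- Slopes 2 and 0: average 1, modification 2.
- Slopes +1 and −1: average 0, modification 2.

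A simulation agrees (3,000 runs, N=62, treatment effect 3, residual SD 3.2, standardised factor). Without group, the mean slopes were 1.00, 0.99 and about 0. With group and group × factor added, the interaction estimates averaged −0.02, 2.04 and 1.98 against true values of 0, 2 and 2.

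Fitting the regression in the bandage arm alone would give b_V, which is still prognosis because b_P is missing.

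**3. Pain on pain.** If both pain terms came from the same visit, R² would be 1 and every other coefficient 0. If the predictor is baseline pain and the outcome is later pain, the model is legitimate.

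**4. Precision of the repaired analysis.** Inputs from Power and sample size: difference 3, SD 3.2, two-sided alpha 0.05, power 0.90 (the stated beta of 0.9 read as power), 24 per group, 62 in total.

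- The protocol's figure reproduces: n per group = 2 × [3.2 × (1.960 + 1.282)/3]² = 23.9, so 24, or 48 in all. Allowing for 20% losses, 48/0.8 = 60, against 62 stated.
- Interaction SE per SD of a continuous factor, 1:1 arms: 2σ/√N.
  - N=62: 6.4/7.874 = 0.81.
  - N=48: 6.4/6.928 = 0.92.
- Detectable with 90% power = (1.960 + 1.282) × SE = 3.242 × SE, using unrounded SEs.
  - N=62: 2.6 points per SD.
  - N=48: 3.0 points per SD.
- The 3.2 is the unadjusted SD of a previous sample. If baseline and follow-up scores correlated at 0.5 (an assumption), the residual SD would shrink by √(1 − 0.25) = 0.866, giving about 2.3 (N=62) and 2.6 (N=48).

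**5. Number of estimates.** 3 factors × 2 outcomes × 2 follow-up visits = 12, and more if subscales are entered separately.

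**The case against.** **The regressions may never have been meant for objective 2.** They are introduced as an additional step, and the protocol does not tie them to any objective. This stands as far as it goes: they may be intended as prognostic models. But then no stated analysis at all addresses objective 2.

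**The detail may be in an analysis plan that is not shown.** This holds for the visit at which the psychological scores are taken, a point commonly left to such a plan. It does not hold for the model terms, because the protocol itself lists the predictors and omits those its objective needs.

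**A reader might infer that the pain model is circular, or that the protocol pools the two arms.** The text fixes neither. The same section uses baseline values as ANCOVA covariates, so baseline pain predicting later pain is the natural reading; the defect is an unstated time point. Nor does the protocol say whether the regressions are pooled or run by arm. The conclusion does not depend on this, since neither version estimates a difference in treatment effect.

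**A reader might also infer that the trial's main result is at risk.** It is not. Pain and disability are compared between arms by ANCOVA with group and baseline, and that comparison does not use these regressions.

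**Conclusion.** The concern holds in limited form: a declared secondary objective has no stated analysis able to answer it. This rests on the model terms alone and needs no numerical assumption. The unstated time point for pain and the missing coping instrument are separate, lesser defects, and neither is the reason the objective goes unanswered.

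The repair makes the question answerable, but only roughly. The detectable interaction of about 2.6 to 3.0 Roland-Morris points per SD of a factor (90% power, 1:1 arms, residual SD 3.2, N between 62 and 48) is close to the 3-point effect for which the whole trial is sized. It would be somewhat smaller if baseline adjustment lowers the residual SD, so the 3.0 should not be read as a fixed threshold. The results have to be labelled exploratory.

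Severity is SHOULD-FIX: the objective is secondary and its best repair is exploratory.

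**What to change.** Add to Data collection and analysis, in substance:

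> For secondary objective 2, RMQ and NPS at end of treatment and at 6 months will each be analysed by a linear model with group, the baseline value of the outcome, one baseline factor (PCS, FABQ or HAD, each in turn) and group × factor. The NPS models will also include baseline RMQ. The interaction estimate will be reported with its 95% CI. These analyses are exploratory and give at least 12 interaction estimates.

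Baseline RMQ is added in the NPS models because allocation is balanced on baseline disability, and RMQ is the disability measure listed. In the RMQ models it is already present as the baseline outcome.

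Keep the eight-variable regressions only as prognostic models, named as such, with all predictors, including pain, taken at baseline and the outcome visit stated.

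Reconcile Objectives with the abstract and Outcome measures on coping: either name an instrument or remove coping from the objective. PCS is listed for catastrophizing, which the objective names separately, so it does not fill this place by default.

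Apart from the coping choice, the cost is wording only. PCS, FABQ and HAD are already collected, and sample size, allocation and the primary comparison do not change. If a coping instrument is added, the cost is one more questionnaire, to be in place before baseline assessments.
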